#### Experimental interventions

Adapted CBT-CP (CBT for Chest Pain)

This will be given by staff trained and supervised by HT. This is similar in several ways to cognitive behaviour therapy for health anxiety (CBT-HA) [8] and its essential features are(i) A formulation made for a recent episode of chest pain with its central fear associations and possible consequences (by end of first session),(ii) assessment of the behaviours that are maintaining the chest pain,(iii) introducing the Beck equation of likelihood times awfulness divided by coping skills times rescue factors (a much larger issue for chest pain than for most other symptoms),(iv) building up a model of the cognitive theory of emotion with illustrations where necessary of the nature of symptoms,(v) introducing the model of fear of having heart disease/more serious heart disease (in those with pre-existing cardiac pathology) versus actually having heart disease/more serious heart disease,(vi) introducing the pie chart and pyramid systems for interpreting other worrying but innocuous symptoms,(vii) trying to influence the over-developed sense of responsibility that the patient feels is necessary to monitor the progress of, and likely interventions for, the chest pain,(viii) using the patient's strengths in finding alternative strategies of dealing with chest pain,(ix) developing a strategy for managing risk (highly important in this population),(x) diary homework to illustrate the relationship between symptoms and events likely to provoke anxiety.

In preliminary work we have found in some cases only one or two sessions of 50–60 min are needed to complete treatment but in others many more sessions are needed, particularly if the chest pain has become chronic.

#### Standard care

This constitutes the care that is currently given to patients in primary and secondary care at present; this involves appropriate testing, explanation of findings, reassurance of the implications of these and the opportunity for the patient to ask questions about the symptoms and the test results.

#### Economic analysis

The economic evaluation will take a health care perspective and, using the service use data collected over follow-up, will calculate the total cost of the services used by each study participant. These costs will be taken together with the cost of the CBT to generate average costs for each randomised group. These costs will be compared using standard t-tests, which are recommended for economic analysis because they allow for analysis of mean costs without transformation. The robustness of this approach will be checked through the calculation of bootstrapped confidence intervals [18, 19]. A cost-utility analysis will also be carried out where the costs in the CBT-CP and ST groups will be compared alongside the difference in QALYs, derived from the EQ-5D.

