## Methods/design

The design is a two-arm parallel design randomized controlled trial carried out in three centres that compares a modified form of cognitive behaviour therapy for chest pain (CBT-CP) that also includes elements of a similar successful treatment for health anxiety (CBT-HA [8] that has been found to have lasting benefit in reducing symptoms, as well as showing superiority for nurse-delivered treatment [9].

The study has two major research questions:does an adapted form of cognitive behaviour therapy for non-cardiac chest pain given between 2 to 6 sessions, lead to reduced anxiety over health over 6 months and one year?does this adapted form of cognitive behaviour therapy reduce health service costs over a period of one year?

These hypotheses, together with related secondary ones, are being tested in a two-arm parallel randomised controlled trial of 2–6 sessions of cognitive behaviour therapy for chest pain (CBT-CP) or standard treatment (ST) in patients presenting with non-cardiac chest pain to cardiology settings who have presented at least once before in the previous year and do not have cardiac pathology of sufficient severity to explain the symptoms.

Our previous work has suggested that most of these patients can be treated successfully in a relatively short number of sessions with an adapted form of cognitive behaviour therapy (CBT), although a minority of handicapped patients may need more. The randomisation was carried out by an independent Clinical Trials Unit (Health Services Unit, CHaRT, University of Aberdeen with equal allocation to CBT and ST, with initial help given from Open-CDMS, a similar independent unit. Standard treatment (ST) will consist of normal management at the clinics concerned, consisting of investigative procedures to exclude pathology and feedback to patients about the findings.

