Assessments of outcome include reduction in health anxiety recorded with the Health Anxiety Inventory [10] (primary outcome at 6 months), and Lucock Health Anxiety Questionnaire [11] adapted with agreement of the author for chest pain, self-completed analog ratings of both the frequency and severity of chest pain and discomfort developed with the aid of a patient (Inskip Scale), self-ratings of generalised anxiety and depression (using the HADS scale) [12], social functioning using the Social Functioning Questionnaire (SFQ) [13], The Schedule for Evaluating Persistent Symptoms (SEPS) [14, 15], that has been found in preliminary studies to be an accurate measure of medically unexplained symptoms, and quality of life using the EQ-5D scale [16] six months and one year (all secondary outcomes). In addition, all health service related costs will be recorded in the 6 months before randomisation and at 6 month intervals subsequently until one year and the costs for patients in the two arms of the trial compared.

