#### Primary and secondary outcomes

The primary outcome is the reduction in scores on the Health Anxiety Inventory between baseline and 6 months, Secondary outcomes are (i) the reduction in visual analog scores of frequency and intensity of chest pain, (ii) reduction in Lucock scores, (iii) reduction in the total SEPS score, (between baseline and 6 months and one year, (ii) the number of attendances at Accident & Emergency Departments after 6 months and one year, (iii) total health service costs in primary and secondary care at 6 and 12 months, (iv) reduction in generalised anxiety symptoms (on the HADS-Anxiety Scale after 6 months and 1 year, (v) reduction in depressive symptoms on the HADS-Depression Scale at the same time points, and (vi) change in mean Lucock scores from baseline after one year.

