#### Analyses

All analyses will be by intention to treat, analysed as randomised. The primary analysis will compare mean change scores of the Health Anxiety Inventory scale from the baseline to 6 months between the treatment and control groups. We shall conduct sensitivity analyses to examine data missing mechanism to decide whether imputation approaches are necessary. Random effects regression model will be used to estimate and test differences of mean change scores between the two comparison groups at 6 and 12 months simultaneously with adjustment for baseline score and key variables used for minimisation procedure. We shall also examine distribution of the outcome score. If a skewed distribution such as a Poisson one was shown, data transformation such as logarithmic transformation of raw data will be carried out before any statistical analysis.

Analyses of secondary outcomes will follow the same analytic procedure and statistical approaches. Economic analysis will follow a similar methodology except that wherever possible data will be analysed without transformation and using bootstrapping techniques for skewed data [18, 19].

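### The Economic analysis section fixes a t-test for costs that cannot use prior cost or centre, while the Analyses section points to a baseline-adjusted model; the two need reconciling, preferably in favour of adjustment

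*Protocol article*

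**What the plan says.** The second major research question in Methods/design asks: "does this adapted form of cognitive behaviour therapy reduce health service costs over a period of one year". The same section says that "all health service related costs will be recorded in the 6 months before randomisation" and at 6-month intervals afterwards up to one year.

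The Economic analysis section builds each patient's total from service use over follow-up, adds the cost of the therapy, and then states: "These costs will be compared using standard t-tests". Its reason is that the t-test lets mean costs be analysed untransformed. It continues: "The robustness of this approach will be checked through the calculation of bootstrapped confidence intervals". It gives the pre-randomisation costs no role. For the cost-utility analysis, costs in the two groups "will be compared alongside the difference in QALYs, derived from the EQ-5D"; nothing is said about adjustment either way.

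The Analyses section describes a random effects regression that adjusts for the baseline score and for the variables used in what it calls minimisation. The Randomisation section describes permuted blocks and names centre as the only stratification factor. Analyses then applies the same procedure to secondary outcomes, and Primary and secondary outcomes lists "total health service costs in primary and secondary care at 6 and 12 months" among these. Analyses ends: "Economic analysis will follow a similar methodology except that wherever possible data will be analysed without transformation", with bootstrapping for skewed data as the other stated exception.

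**The concern.** Two analysts could follow this article faithfully and report different cost results. One would run a t-test on follow-up cost. The other would fit a regression adjusted for prior cost, because the exceptions that Analyses names for economic data concern transformation and bootstrapping, not dropping the baseline covariate. A choice left open on one of two major questions can be settled after the results are seen.

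If the t-test governs, useful information is discarded. Past cost plausibly predicts later cost in patients selected for repeat presentation. The Procedure section says that the chest pain pathway differs between the three hospitals, so cost may differ by centre too. The bootstrap check does not help here: it addresses skewness, not imbalance. Nor does the stated reason for the t-test require it, since linear regression on untransformed cost also compares mean costs.

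**Working it through.** **The plan's own figure.** The article gives no figure for the economic comparison. Its only sample size is for the Health Anxiety Inventory: difference 4, SD 6.0, 90% power, two-sided 5%. Per arm, n = 2 × 6² × (1.960 + 1.282)² / 4² = 47.3, so 48 per arm and 96 in total. This reproduces the stated 96.

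**Inputs.** Recruited: 68 (Status of the trial). Allocation is equal (Methods/design), so 34 per arm is assumed. The article gives no correlation ρ between prior and follow-up cost; 0.3, 0.5 and 0.7 are assumptions. Results are in SD units under a normal approximation. They ignore missing data and the small loss of degrees of freedom from covariates.

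**Chance imbalance in prior cost.**
- SD of the between-arm difference = √(2/34) = 0.243 baseline SDs.
- 95% limits: ±1.96 × 0.243 = ±0.475 SD.
- Probability that it exceeds 0.25 SD in either direction: 0.25/0.243 = 1.03, which gives about 30%.

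**What reaches the cost difference.** Only the fraction ρ of the imbalance is carried over. The adjusted standard error is the unadjusted one times √(1 − ρ²), and the equivalent unadjusted trial size is 68/(1 − ρ²).

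| ρ (assumed) | SD of carried-over imbalance, ρ × 0.243 | SE unadjusted | SE adjusted | CI narrower by | Equivalent unadjusted N |
|---|---|---|---|---|---|
| 0.3 | 0.073 | 0.243 | 0.231 | 5% | 75 |
| 0.5 | 0.121 | 0.243 | 0.210 | 13% | 91 |
| 0.7 | 0.170 | 0.243 | 0.173 | 29% | 133 |

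**Given an imbalance d.** The bias of the t-test estimate is ρ × d. Under no effect, its z statistic has mean ρd/0.243 and SD √(1 − ρ²).
- d = 0.25 SD: bias 0.075, 0.125 and 0.175 SD; conditional type I error about 5%, 5% and 4%.
- d = 0.48 SD (about the 95% limit): bias 0.144, 0.240 and 0.336 SD; conditional type I error about 8%, 13% and 21%.

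Averaged over all randomisations, the t-test's type I error remains 5%.

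**Side by side.** Economic analysis names a test that takes no covariate. Analyses extends a covariate-adjusted model to costs twice: once through the rule for secondary outcomes, and once through the sentence on economic analysis. The two sections cannot both describe the main cost analysis.

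**The case against.** The best defence is that the specific text governs the general one. On that view the Economic analysis section settles the cost method, and similar methodology in Analyses is only a loose description. The t-test on mean cost is valid: over repeated randomisations it is unbiased and holds its 5% error rate. If ρ is only 0.3, adjustment narrows the CI by just 5%. An article also condenses a fuller plan, where the economic model may be set out.

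The validity of the t-test stands, and so does the modest gain at the low end. The rest does not dispose of the point. The cost method is stated here rather than left to another document, and so is the sentence that conflicts with it.

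A reader might infer more than the text supports, in four ways:
- That the plan has settled on unadjusted costs. It has not, because Analyses points the other way.
- That QALYs will be compared as a raw difference. The article does not say so, and the detail may properly lie elsewhere.
- That a QALY imbalance would affect the second research question. That question concerns costs only; QALYs belong to the cost-utility analysis.
- That baseline imbalance passes in full into the cost result. Prior cost is not part of follow-up cost, so only the fraction ρ does.

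**Conclusion.** The point holds as an internal conflict together with an avoidable loss of precision. It does not show that the cost comparison is invalid. At 68 patients, prior-cost imbalance has an SD of about 0.24 baseline SDs. Not using prior cost forgoes a CI about 5% to 29% narrower, and leaves the estimate conditionally biased if the arms happen to differ.

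The inflation of conditional type I error appears only with a large imbalance: 8% to 21% near the 95% limit, and none at 0.25 SD. These sizes rest on an equal split, assumed correlations of 0.3 to 0.7 and a normal approximation to costs that are probably skewed. The conflict between the sections rests on none of these assumptions. For QALYs, the most that can be said is that adjustment is unspecified. The change should be made.

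**What to change.** Reconcile Economic analysis with Analyses in one statement of the cost model. Status of the trial reports that no data had been examined, so this can be done without knowledge of results.

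- **Main cost analysis:** linear regression of untransformed 12-month cost on arm, cost in the 6 months before randomisation, and centre, with non-parametric bootstrap CIs. This keeps the stated aim of comparing mean costs untransformed.
- **Sensitivity analysis:** the t-test as now written.
- **Cost-utility analysis:** state that the QALY difference is adjusted for centre and for baseline EQ-5D. The article lists EQ-5D at six months and one year and says only in general terms that ratings are recorded at baseline, so first confirm that baseline EQ-5D was taken. Bootstrap costs and QALYs jointly, by patient within arm.

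The price is a change of wording and slightly more programming. The prior costs are already among the data to be recorded.

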#### Primary and secondary outcomes

The primary outcome is the reduction in scores on the Health Anxiety Inventory between baseline and 6 months, Secondary outcomes are (i) the reduction in visual analog scores of frequency and intensity of chest pain, (ii) reduction in Lucock scores, (iii) reduction in the total SEPS score, (between baseline and 6 months and one year, (ii) the number of attendances at Accident & Emergency Departments after 6 months and one year, (iii) total health service costs in primary and secondary care at 6 and 12 months, (iv) reduction in generalised anxiety symptoms (on the HADS-Anxiety Scale after 6 months and 1 year, (v) reduction in depressive symptoms on the HADS-Depression Scale at the same time points, and (vi) change in mean Lucock scores from baseline after one year.

#### Analyses

All analyses will be by intention to treat, analysed as randomised. The primary analysis will compare mean change scores of the Health Anxiety Inventory scale from the baseline to 6 months between the treatment and control groups. We shall conduct sensitivity analyses to examine data missing mechanism to decide whether imputation approaches are necessary. Random effects regression model will be used to estimate and test differences of mean change scores between the two comparison groups at 6 and 12 months simultaneously with adjustment for baseline score and key variables used for minimisation procedure. We shall also examine distribution of the outcome score. If a skewed distribution such as a Poisson one was shown, data transformation such as logarithmic transformation of raw data will be carried out before any statistical analysis.

Analyses of secondary outcomes will follow the same analytic procedure and statistical approaches. Economic analysis will follow a similar methodology except that wherever possible data will be analysed without transformation and using bootstrapping techniques for skewed data [18, 19].

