**Methods/design:**

A two-arm parallel controlled randomized trial of standard care versus a modified form of cognitive behaviour therapy for chest pain (CBT-CP) in patients who have attended emergency hospital services. Inclusion criteria include (i) emergency attendance more than once in the previous year with chest pain when no physical pathology has been found, (ii) aged between 16 and 75, (iii) signed consent to take part in the study. Exclusion criteria are (i) under current psychiatric care, (ii) those who have had new psychotropic drugs prescribed within the last two months, (iii) are receiving or about to receive a formal psychological treatment. Those satisfying these criteria will be randomized to 4–10 sessions of CBT-CP or to continue with standard care.

Participants are randomized using a remote web-based system using permuted stacked blocks stratified by study centre. Assessment is carried out at baseline by researchers subsequently masked to allocation and at 6 months and 1 year after randomization. The primary outcome is the Health Anxiety Inventory score at 6 months, and secondary outcomes are generalised anxiety and depressive symptoms, the Lucock Health Anxiety Questionnaire adapted for chest pain, visual analogue scales for chest pain and discomfort (Inskip Scale), the Schedule for Evaluating Persistent Symptoms (SEPS), health related quality of life, social functioning and medical resource usage. Intention to treat analyses will be carried out with clinical and functioning data, and a cost-utility analysis will compare differences in total costs and differences in quality of life using QALYs derived from the EQ-5D. The data will also be linked to another parallel study in New Zealand where 126 patients with the same inclusion criteria have been treated in a similar trial; the form of analysis of the combined data has yet to be determined.

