#### Randomisation

Patients who are identified as eligible for the trial by cardiology and accident and emergency staff, and willing to take part, were first assessed by an independent research assistant. After baseline assessment all ratings and demographic details are recorded on a secure on-line data base, initially Open-CDMS in London and from 2014, CHaRT in the Health Services Research Unit, University of Aberdeen. Patients are then allocated to either CBT-CP or standard care in permuted stacked blocks (do we specify numbers) stratified by study centre. The allocated treatment is then passed to the trial coordinator (SC) who, if the patient is allocated to CBT-CP, informs the next available therapist at the centre concerned and then the patient, GP and consultant. Patients allocated to standard care are informed by letter or phone call and the GP and hospital team also notified. Follow up assessments are carried out by research assistants ignorant of original allocation after 6 and 12 months. All data are kept by CHaRT until the termination of the trial.

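### The regression model's covariates are tied to a minimisation procedure the protocol never describes, and study centre, the only stated stratification factor, is not named

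*Protocol article*

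**What the plan says.** Two places in the protocol article describe allocation, and they agree. The Abstract (Methods/design) states: "Participants are randomized using a remote web-based system using permuted stacked blocks stratified by study centre". The Randomisation section repeats the method and the single factor, and still carries an unresolved drafting query: "permuted stacked blocks (do we specify numbers) stratified by study centre". The main Methods/design section describes a "randomized controlled trial carried out in three centres", "with equal allocation to CBT and ST".

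The Analyses section opens with the primary comparison: "The primary analysis will compare mean change scores of the Health Anxiety Inventory scale from the baseline to 6 months". It then gives the model: "Random effects regression model will be used to estimate and test differences of mean change scores between the two comparison groups at 6 and 12" (the two follow-up times, in months, fitted jointly). Its covariates are given as "adjustment for baseline score and key variables used for minimisation procedure". Secondary outcomes are to follow the same approach, while the economic analysis has its own rules. The section does not mention centre as a covariate, a stratum or a random effect, and it does not say what the random effects are.

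**The concern.** Minimisation and stratified permuted blocks are different ways of allocating patients. An adjustment set defined as the variables of one cannot be read off a trial described as using the other. A statistician working from this text could include nothing beyond baseline, could include centre, or could include some other variables taken to be the ones meant.

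The adjustment matters because stratified allocation balances the arms within centres. If outcome differs between centres, an analysis that ignores centre leaves that variation in the error term although the design has already removed it from the treatment comparison. The reported standard error is then too large and the test rejects too seldom.

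Some centre effect is plausible. The Procedure section says the chest pain pathway differs between the three hospitals, and standard treatment is each clinic's normal management. The trial also has little precision to spare, having recruited 68 patients against a target of 96.

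**Working it through.** **1. The plan's own figure.** The inputs are in the target-number section: difference 4 HAI points, SD of change 6.0, two-sided 5%, power 90%, with 1:1 allocation from Methods/design.

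n per arm = 2 × (1.960 + 1.282)² × 6.0² / 4² = 2 × 10.51 × 2.25 = 47.3, rounded up to 48, so 96 in total. Power at 48 per arm is 90.4%. The stated 96 reproduces, and this point does not change it.

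**2. The passages side by side.**

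| Place | Allocation method | Factors named |
|---|---|---|
| Abstract, Methods/design | Stratified permuted blocks | Study centre |
| Randomisation | Stratified permuted blocks | Study centre |
| Analyses | Minimisation | None |

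The third row conflicts with the first two, and nothing else in the document resolves it.

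**3. Size, by formula.** Let R² be the share of outcome variance that centre explains after baseline adjustment. With arms balanced within centres, omitting centre multiplies the reported standard error by about 1/√(1 − R²). The document gives no R², so the range is assumed.

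| Assumed R² | SE multiplier | 68 × (1 − R²) |
|---|---|---|
| 0 | 1.000 | 68.0 |
| 0.05 | 1/√0.95 = 1.026 | 64.6 |
| 0.15 | 1/√0.85 = 1.085 | 57.8 |

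The last column is the number of patients whose information the reported precision would reflect. The shortfall is 3.4 to 10.2 patients over the assumed 5% to 15%.

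**4. Size, by simulation.** There were 4,000 runs per scenario, with three near-equal centres, permuted blocks of 4 within centre, total SD 6 and a linear model at one time point. Block size, centre sizes and centre share are assumptions. Results for N = 68:

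| Centre share of variance | Type I error, without / with centre | Power at 4 points, without / with centre |
|---|---|---|
| 0 | 4.4% / 4.2% | 77% / 76% |
| 5% | 4.9% / 5.4% | 79% / 80% |
| 10% | 3.8% / 5.1% | 79% / 82% |
| 20% | 3.2% / 5.3% | 79% / 85% |

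At N = 96 and a 20% share, type I error was 2.9% without centre and 5.4% with it, and power was 92% and 95%. Simulation error on a 5% rate is about √(0.05 × 0.95 / 4000) = 0.3 percentage points, so the differences at 0 and 5% are close to noise. Those at 10% and 20% are not.

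**5. Cost of including centre.** Three centres need two indicator variables. In a single-time-point regression on 68 patients with intercept, arm and baseline, residual degrees of freedom go from 68 − 3 = 65 to 68 − 5 = 63.

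**The case against.** The strongest reply is that this is a slip of terminology. The authors clearly mean to adjust for whatever governed allocation, and the only such variable they name is centre. On that reading centre is in the model under the wrong label. The random effects are also unnamed, so centre is not excluded there either. This stands as far as it goes. A reader might infer that centre has been left out, or that the covariate set is empty, but the text supports only that centre is not named and that the set is tied to an undescribed procedure.

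Nor can the document settle which passage is wrong. Two data systems were used, with a change in 2014, so minimisation in one period cannot be ruled out, although both descriptions of allocation say blocks.

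A reader might also infer that covariates will be picked after the results are seen. The document does not show that: the list may be fixed in an analysis plan that is not at hand, and the status section says no data had been examined. The absence of a list is not the fault. The fault is a stated rule that conflicts with the stated design, and a separate plan written to follow this rule would inherit the conflict.

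Finally, it is an inference to call this the primary model. The section defines the primary analysis as the 6-month comparison of mean change, and the covariates are attached to the joint 6- and 12-month model that follows.

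**Conclusion.** The contradiction is real and should be fixed. The Analyses section ties the model's covariates to minimisation, while the Abstract and Randomisation section describe only permuted blocks stratified by centre, and centre is not named in the analysis.

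The consequence is modest and conditional. If centre is in fact omitted and explains 5% to 15% of residual variance, the reported standard error is about 3% to 8% too wide. In the simulation at N = 68, power at 4 points fell by about 3 points at a 10% centre share and 6 points at 20%. With no centre effect the loss is nil. These shares are assumptions. Differing care pathways make a centre effect plausible but do not show that change in health anxiety differs by centre once baseline is adjusted for. The error is in the conservative direction, the treatment estimate is not biased, and the planned 96 is unaffected. This is therefore a correction worth making before data are examined, not a threat to the trial's validity.

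**What to change.** Establish from the randomisation records which method was used in each period, and make the Abstract, Randomisation and Analyses sections agree.

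If stratified blocks were used throughout, replace the minimisation phrase with: *adjustment for baseline score and study centre (the stratification factor)*. Apply this to the 6- and 12-month HAI model and to the clinical secondary outcomes analysed in the same way. Do not extend it to total health service costs: these are listed as a secondary outcome, but the Economic analysis section specifies t-tests checked by bootstrap intervals, and a blanket rule would create a new conflict.

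If minimisation was used in any period, name its variables, correct the two descriptions of allocation, and adjust for those variables as well as centre.

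The cost is a sentence in the Analyses section, matching edits to the allocation text if needed, and two degrees of freedom for three centres. Any minimisation variables would use further degrees of freedom. No additional data are required.

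### A skewness-triggered log transformation would move the primary Health Anxiety Inventory result off the points scale and is a poor method for emergency attendance counts

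*Protocol article*

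**What the plan says.** Under Primary and secondary outcomes the article states: "The primary outcome is the reduction in scores on the Health Anxiety Inventory between baseline and 6 months". The Analyses section matches this: "The primary analysis will compare mean change scores of the Health Anxiety Inventory scale from the baseline to 6 months". The Target number of participants section works in the same unit, with a difference of 4 HAI points (2 being considered), a standard deviation of change of 6.0 and 96 patients.

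The Analyses section then says that the distribution of the outcome score will be inspected. "If a skewed distribution such as a Poisson one was shown", the consequence is that "data transformation such as logarithmic transformation of raw data will be carried out before any statistical analysis". It goes on: "Analyses of secondary outcomes will follow the same analytic procedure and statistical approaches". One of those secondary outcomes is "the number of attendances at Accident & Emergency Departments after 6 months and one year".

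Economic data are treated differently: "wherever possible data will be analysed without transformation and using bootstrapping techniques for skewed data".

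**The concern.** The rule is stated as something that will happen once skewness is seen, so it is more than a detail left for later. It raises three problems.

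- **Primary outcome.** Logging raw HAI scores changes what is estimated. A difference between log scores is a log ratio, so the arm comparison becomes a ratio of proportional changes. Neither 4 nor 2 points can be used to judge it, and the sample size no longer describes the test performed.
- **Trigger.** The rule looks at the distribution of the outcome itself. The regression model's assumption concerns its residuals after adjustment. A skewed outcome does not show that the model fails, yet it would be enough to change the effect measure of the primary analysis. That choice would rest on the trial's own outcome data.
- **Attendance counts.** Counts include zeros, and a plain log of zero does not exist. Adding a constant makes the log computable, but the estimated effect then depends on the constant. A Poisson-like shape is a reason to use a count model.

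**Working it through.** **1. The planned sample size is on the points scale.** Inputs from Target number of participants: difference 4, standard deviation of change 6.0 (stated for 1 year), two-sided 5 %, power 90 %. Equal allocation is stated in Methods/design.

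n per arm = 2 × (1.960 + 1.282)² × 6.0² / 4² = 2 × 10.51 × 36 / 16 = 47.3, rounded up to 48, or 96 in total. The stated figure is reproduced. On a log scale neither input applies, and the article gives no log-scale standard deviation, so the number cannot be recomputed there.

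**2. What 4 points means on a ratio scale.** The article gives no HAI means, so control means at follow-up are assumed, with equal baselines. Ratio = (control mean − 4) / control mean.

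| Assumed control mean | Ratio for 4 points | Points for a ratio of 0.80 |
|---|---|---|
| 10 | 6/10 = 0.60 | 2 |
| 20 | 16/20 = 0.80 | 4 |
| 30 | 26/30 = 0.87 | 6 |

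One ratio corresponds to 2 points or to 6 depending on level, so a log-scale result cannot be set against a fixed criterion in points.

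**3. Zeros in attendance counts.** The article gives no attendance rate, so a range of means is assumed. Under a Poisson distribution, P(0) = exp(−mean).

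| Assumed mean per period | Share with zero |
|---|---|
| 0.5 | 61 % |
| 1 | 37 % |
| 2 | 14 % |
| 3 | 5 % |

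A plain log is undefined for these patients.

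**4. Dependence on the added constant.** Assume Poisson counts with means 1.0 and 0.5, a true ratio of 0.50. For each constant c, the expected value of log(count + c) is computed in each arm, the difference taken and exponentiated.

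| c | Expected log, mean 1.0 | Expected log, mean 0.5 | Difference | Apparent ratio |
|---|---|---|---|---|
| 0.01 | −1.467 | −2.721 | −1.254 | 0.29 |
| 0.1 | −0.579 | −1.295 | −0.716 | 0.49 |
| 0.5 | 0.169 | −0.210 | −0.378 | 0.685 |
| 1 | 0.573 | 0.314 | −0.260 | 0.77 |

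The same data-generating process therefore gives anything from a 71 % to a 23 % apparent reduction. With assumed means of 2.0 and 1.2 (true ratio 0.60), the apparent ratio runs from 0.34 to 0.73 over the same constants.

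**The case against.** A reader might infer that the rule cannot be carried out at all for the primary outcome, because a change score can be zero or negative, and that patients who do not improve would be lost. The text does not support this. It applies the transformation to raw data before analysis, and raw HAI scores can be logged wherever they exceed zero and then differenced. Patients who do not improve keep their raw scores. The article states no rule that drops anyone.

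Three further defences carry weight. The log is given only as an example, so a square root, which is defined at zero, would also be allowed; only a plain log fails on zero counts. The switch is conditional on skewness, and the Status of the trial section says that no data had been examined, so the rule itself was written beforehand. The article does not say whether the check would be made by arm or on pooled, blinded data, so a reader should not infer an unblinded choice.

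It is also fair that a skewness threshold, the handling of zeros and the exact count model are commonly left to an analysis plan. Their absence is not the point here. The point is a stated rule whose consequence conflicts with the primary analysis stated in the same section. No choice of threshold or blinding removes that conflict once the rule fires. Other transformations, including the square root, also take HAI off the points scale.

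**Conclusion.** The concern holds in a limited form, with moderate confidence. If skewness is judged present, the article commits the trial to an analysis that no longer estimates the difference in mean HAI change in points on which the primary outcome, the 4- or 2-point criterion and the 96 patients all rest. The trigger is the observed outcome distribution and not the model residuals. The same rule reaches emergency attendances, where a plain log fails at zero and a log with a constant can return 0.29 to 0.77 for a true ratio of 0.50.

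The HAI control means, attendance means and Poisson shape are assumptions; the documents supply none of them. At assumed attendance means of 2 or 3 the zero share falls to 14 % or 5 %, so the count problem is smaller there, though the result still depends on the constant at means of 2.0 and 1.2. Whether the rule would be triggered for HAI cannot be known from the article.

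**What to change.** State that the primary HAI analysis and the other scale scores stay on their original points scale whatever skewness is observed. If model residuals are clearly non-normal, keep the model and report robust or bootstrap 95 % confidence intervals. The Economic analysis and Analyses sections already use bootstrapping for skewed costs. Keep any transformed analysis as a sensitivity analysis only.

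Analyse emergency attendances with a count model, for example negative binomial regression with terms for arm and centre and an offset for follow-up time, and report rate ratios with 95 % confidence intervals.

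The cost is a few lines of text and one different standard model. The planned sample size is unaffected, because it was calculated in points. Since the article reports that no data had been examined, the change could be made at that stage without any suspicion of choosing the scale to suit the result.
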